# Combination of Xuesaitong and Aspirin Based on the Antiplatelet Effect and Gastrointestinal Injury: Study Protocol for a Randomized Controlled Noninferiority Trial

**DOI:** 10.1155/2021/5552506

**Published:** 2021-07-13

## Abstract

**Background:**

Aspirin is the first-line medication for prevention and treatment of coronary heart disease (CHD). However, long-term use of aspirin resulting in gastrointestinal mucosal injury and bleeding limits the regularity of medication. Xuesaitong is a marketed Chinese medicine contained main active component in Panax notoginseng saponins (PNS), which can significantly inhibit platelet aggregation in patients with CHD. Our previous studies have already showed that PNS could reduce the gastrointestinal mucosal injury caused by aspirin in preclinical study. However, there is a need for further clinical studies to evaluate synergy and attenuation effect of the combination.

**Methods:**

This trial is a prospectively planned, open-labeled, parallel-grouped, single-centered clinical trial. A total of eligible 480 participants will be randomly allocated into three groups: aspirin group, Xuesaitong group, and drug combination group at a ratio of 1 : 1 : 1. The primary outcome is the change of platelet aggregation rate and calprotectin activity. Secondary outcomes include PAC-1, P-selectin, P2Y12, I-FABP activity, and fecal occult blood. *Discussion*. The results of the study are expected to provide evidence of high methodological and reporting quality on the synergy function of Xuesaitong and aspirin upon the antiplatelet and anti-gastrointestinal injury effect for CHD. It also provides an experimental basis for clinical rational drug combination therapy. *Trial Registration*. This trial was registered in the Chinese Clinical Trail Registry, ChiCTR2000036311, on 22 August 2020, http://www.chictr.org.cn/edit.aspx?pid=58798&htm=4.

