### 2.10. Data Management and Statistical Analysis Plan

We use EDC system to collect the data. The system administrator establishes the eCRF and conducts logic verification and range checks for data values. Two investigators fulfill double-data entry.

The analysis will be performed in a modified intention-treat population, which included all randomized participants who received at least one dose of Xuesaitong or aspirin. Continuous variables are presented as the mean ± SD and categorical variables as number and percentage. Comparisons between treatment groups were assessed using Student's *t*-test or Wilcoxon rank-sum test for continuous variables. Comparisons were assessed using the Fisher exact test for categorical variables. Data for patients who were lost to follow-up were censored at the time of the last contact. A multivariable Cox proportional-hazards regression analysis that included center and treatment as independent variables was conducted, and the results are expressed as hazard ratio (HR) with 95% confidence interval (CI). The incidence of adverse events was compared using the chi-squared test. *P* < 0.05 (two-sided) was considered to be statistically significant. All analyses were conducted using SPSS software 26.0.

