(1) Serious adverse events occur or having obvious abnormal value of the laboratory tests
(2) The investigators believe someone's trial needs to be terminated because of medical, safety, or GCP considerations
Trial termination
(1) Half of the participants have mild adverse events other than gastrointestinal reactions
(2) The investigators believe it is necessary to abort the trial for medical or safety purposes

**Table 3 tab3:** Dose and duration of medication.

Group	Medication	Dose and method	Duration
Aspirin group	Enteric-coated aspirin	100 mg, q.d., oral	30 days
Xuesaitong group	Xuesaitong soft capsule	200 mg, t.i.d., oral	30 days
Drug combination group	Xuesaitong soft capsule + enteric-coated aspirin	100 mg q.d. oral aspirin and 200 mg t.i.d. oral Xuesaitong soft capsule	30 days

**Table 4 tab4:** Clinical outcomes of the trial.

Items
*Primary outcomes*
Primary outcomes of improving efficacy
Platelet aggregation rate (platelet aggregation analyzer)
Primary outcomes of reducing gastrointestinal side effects
Change in calprotectin activity (ELISA) [17]

*Secondary outcomes*
Secondary outcomes of improving efficacy
(1) Change in PAC-1 activity (flow cytometry)
(2) Change in P-selectin activity (flow cytometry)
(3) Change in P2Y12 acceptor activity (flow cytometry)
Secondary outcomes of reducing gastrointestinal side effects
(1) Change in I-FABP activity (ELISA) [18]
(2) Change in fecal occult blood

*Safety outcomes*
(1) Serum biochemistry
(2) Blood routine
(3) Urine routine
(4) Stool routine
(5) ECG

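### Two primary outcomes and three arms, with two-group tests each at 0.05, but no primary contrast and no either/both rule; the outcome and contrast used for sizing do not match the stated aim

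*Protocol article*

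**What the plan says.** **Outcomes.** The abstract names two quantities under a singular label: "The primary outcome is the change of platelet aggregation rate and calprotectin activity". Table 4 lists one under "Primary outcomes of improving efficacy" (platelet aggregation rate) and the other under "Primary outcomes of reducing gastrointestinal side effects" (calprotectin). Section 2.4, however, treats platelet aggregation rate as the only primary outcome.

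**Arms.** Participants are "randomly allocated into three groups: aspirin group, Xuesaitong group, and drug combination group at a ratio of 1 : 1 : 1".

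**Aim and contrast.** The last paragraph of the Introduction asks whether the combination is better than using one drug, in a trial that it and the title both call noninferiority. Section 2.4 assumes 38.72% for aspirin and 37.79% for Xuesaitong, and gives no value for the combination.

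**Tests.** Section 2.10 says: "Comparisons between treatment groups were assessed using Student's *t*-test or Wilcoxon rank-sum test for continuous variables". The threshold is P "< 0.05 (two-sided) was considered to be statistically significant". No pair of arms is named.

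**The concern.** Four statements together should identify the primary claim, and they disagree. Two outcomes are primary in the abstract and Table 4, but one in Section 2.4. The aim concerns the combination, but the sizing concerns the two single drugs. The title says noninferiority, but the aim is worded as superiority. The analysis section then sets a per-test level of 0.05 with two-group tests for three arms.

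A team following this text could test several pairs on two outcomes and call any significant one a primary result. The question that motivates the trial is whether adding Xuesaitong to aspirin keeps the antiplatelet effect and lessens gut injury. It could be displaced by an easier contrast. For example, participants enter after at least a year on aspirin (Table 2), and the Xuesaitong arm receives no aspirin (Table 3). The protocol names aspirin as the cause of the injury, so a calprotectin difference between the two single-drug arms could arise from stopping aspirin and would say nothing about the combination. For the same reason, beating Xuesaitong alone on calprotectin is not a result the combination should be expected to deliver, so superiority to each single drug on both outcomes is a poorly formed target.

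**Working it through.** **The plan's own figure.** Section 2.4 gives 131 per arm at alpha 0.05 and 80% power, then 160 enrolled for 20% dropout. No SD and no margin are printed, so 131 cannot be reproduced. Read as superiority on the stated difference, 38.72 − 37.79 = 0.93 points, the implied SD is 0.93 × √(131/2) / (1.960 + 0.842) = 2.7 points (two-sided). For dropout, 131/0.8 = 164 and 131 × 1.2 = 158, both close to 160. Whatever SD or margin was used, the calculation refers to one outcome and to a contrast other than the one in the aim. It makes no allowance for a second outcome or further contrasts.

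**Number of possible primary tests.** Three arms give 3 pairs, and 3 × 2 outcomes = 6. The Introduction's aim, read as combination against each single drug, gives 2 × 2 = 4. Combination against aspirin alone gives 1 × 2 = 2. The document does not say which applies.

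**Chance of at least one false primary result.** Assumptions: all arms truly equal on both outcomes, equal arm sizes, normal test statistics, two-sided 0.05 per test, and any one significant result counts. The correlation between outcomes is not given, so it is varied from 0 to 0.8. Pairs sharing an arm are correlated 0.5 in size, and this is built into the simulation (2,000,000 draws per setting).

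| Tests that count | corr. 0 | 0.3 | 0.5 | 0.8 |
|---|---|---|---|---|
| All 6, either direction | 22.9% | 22.4% | 21.3% | 18.5% |
| 4 combination contrasts, either direction | 17.3% | 16.9% | 16.1% | 14.0% |
| Combination vs aspirin, either outcome, either direction | 9.8% | 9.5% | 9.1% | 7.9% |
| 4 combination contrasts, only results favouring the combination | 8.9% | 8.5% | 8.1% | 6.9% |
| Combination vs aspirin, either outcome, only favouring the combination | 4.9% | 4.8% | 4.5% | 3.9% |

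Checks at correlation 0:
- Three pairs on one outcome give 12.2%, so six tests give 1 − (1 − 0.122)² = 22.9%.
- Two contrasts sharing the combination arm give 9.06% on one outcome, so four tests give 1 − (1 − 0.0906)² = 17.3%.
- Treating all six as independent would give 1 − 0.95⁶ = 26.5%, which is too high because the pairs share arms.

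**If both outcomes must succeed on one contrast.** The error is at most 5%, because a false claim needs a false rejection on an outcome that is itself tested at 0.05.

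**Joint power under that rule.** With each outcome at 80% (assumed), the power for both is 0.8 × 0.8 = 64% at correlation 0 and 69% at correlation 0.5 (bivariate normal).

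**The case against.** A reader might infer that six tests are planned and that the false-claim rate for the combination is about 22%. The documents do not support that. Section 2.10 lists no pairs, and aspirin against Xuesaitong is not part of the Introduction's aim. The 22% counts rejections in both directions, including those where the combination does worse, and those cannot support the aim. It also presumes equality of all arms on calprotectin, which is hard to believe when one arm receives no aspirin. Restricted to results favouring the combination, the figure is 7–9% for four contrasts and just under 5% for combination versus aspirin, which is twice the 2.5% that a single two-sided 0.05 test allows in the favourable direction.

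A benign reading also exists. The abstract joins the two outcomes with 'and', and Table 4 gives each its own purpose, which is consistent with requiring both. Under that rule on one contrast the error would be controlled. Nothing in the text adopts it, but nothing adopts an any-one-counts rule either.

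Finally, hierarchy and success rules are often left to the SAP or full protocol, neither of which is shown, so their absence alone would be no finding. What stands is what the article itself fixes: the two-group tests at 0.05 for three arms, and the conflicts over which outcome is primary, which contrast matters, and whether the trial asks about noninferiority or superiority. A later document cannot settle these without departing from one of the published statements.

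**Conclusion.** The point holds as a conflict in the definition of the primary claim, with multiplicity as its consequence. The inflation is conditional: at most about 23% if all six pairwise tests count, about 14–17% for the four combination contrasts (correlation 0 to 0.8), and about 7–9% if only results favouring the combination count. All of these assume the global null and that one significant result is enough. They describe the superiority-type tests in Section 2.10; no noninferiority margin is printed, so no corresponding rate can be given for a noninferiority test. The 23% is an upper bound and should not be quoted as the trial's error rate. The defect should be corrected, and it does not depend on the count of six.

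**What to change.** 1. Name combination versus aspirin as the primary comparison.
2. Require both platelet aggregation and calprotectin to succeed, each tested at its full level with no alpha split.
3. State for each outcome whether the test is noninferiority or superiority, and reconcile the title with the aim in the Introduction. Any noninferiority test needs its margin stated.
4. Test combination versus Xuesaitong on platelet aggregation only after both primary results are met. Report all other pairs descriptively with 95% confidence intervals.
5. Rewrite Section 2.4 so that its outcomes and contrast match points 1 and 2, and restate the power.

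Points 1 to 4 are changes of wording. The cost is fewer confirmatory claims and joint power below the stated 80%: about 64–69% under the assumptions shown above. Whether the planned number is still enough is a sample-size question to be answered with a stated SD for each outcome and a calprotectin effect, none of which the article gives. The alternative of keeping all six tests with a Bonferroni split (0.05/6 = 0.0083 each) would need about 1.54 times the sample per arm for 80% power on each test: ((2.638 + 0.842)/(1.960 + 0.842))² = 1.54.

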## 1. Introduction

Coronary heart disease (CHD) is the leading cause of death worldwide, with more than 1.5 million deaths each year [1, 2]. Aspirin is a well-known baseline antiplatelet agent, serving as the first choice for the prevention and treatment of CHD. However, many studies have shown that the long-term administration of aspirin has the potential for significant side effects on the gastrointestinal tract causing mucosal lesions, bleeding, or peptic ulcers [3]. Although enteric-coated aspirin have been developed, 10%–25% long-term users still got peptic ulcers [4] and aspirin increases the risk of gastrointestinal bleeding by almost 3-fold [5]. These side effects limit the regularity of medication which increases the risk of cardiovascular accidents. Therefore, it is particularly important to prevent the occurrence of aspirin-induced gastrointestinal injury. While proton pump inhibitor (PPI) preparations are usually recommended to prevent aspirin-induced gastrointestinal injury [4], especially for the elderly, the application of PPI damages the phospholipid layer in intestinal mucus, which may protect gastric mucosa but increase the risk of small intestinal injury [6]. Therefore, it is urgent to find a strategy to reduce aspirin-induced gastrointestinal injury.

Xuesaitong capsule is a marketed Chinese medicine with components of Panax notoginseng saponins (PNS), which is a mixture of ginsenosides Rb1, Rg1, Rd, Re, and notoginsenoside R1. It has been used in combination with aspirin in preventing cardiovascular disease for several years with a good clinical effect [7, 8]. Our previous study has indicated that the combination could inhibit platelet activation caused by blood hypercoagulability and reduce platelet aggregation to prevent thrombosis [9, 10]. These effects may rely on another finding from our team, which shows that aspirin and Xuesaitong could increase the area under the curve (AUC) and promote the absorption of each other [11, 12]. More interestingly, our research also found Xuesaitong attenuates expression of aspirin-induced tight junction protein and apoptosis of crypt epithelial cells in small intestine [13]. It means Xuesaitong may serve as a pharmacological treatment for aspirin-induced gastrointestinal injury. Since the dual-directional regulation of Xuesaitong, it became the potential combination therapy to solve the clinical dilemma. All the preclinical evidences have elucidated the combination could enhance aspirin's efficacy and decrease aspirin-induced gastrointestinal injury. However, it still lacks high-level clinical evidence.

In this study, we conducted a randomized controlled noninferiority trial to explore whether the efficacy and safety of combination for CHD patients are superior to the single use.

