## 2. Methods

### 2.1. Study Design and Setting

This is a prospectively planned, open-labeled, parallel-grouped, single-centered clinical trial. The trial will be conducted at the outpatient care of the Cardiology Department at the Dongzhimen Hospital, Beijing University of Chinese Medicine in China. The staff of the department will be informed of the trial and they will help researchers to recruit participants. The trial is conducted by the ethical principles laid down in the Declaration of Helsinki, the Guideline for Good Clinical Practice, and local laws. The informed consent form will be obtained from all participants before any trial-related procedures were conducted, enrolled after a complete and extensive description of the study. The trial was approved by the Ethics Committee of Dongzhimen Hospital, Beijing University of Chinese Medicine (Supplementary File 1). We present the protocol in accordance with the SPIRIT reporting checklist (Standard Protocol Items Recommendations for Interventional Trials) (Supplementary File 2).

In terms of research methods, we refer to and improve one of our previous experimental designs [14]. 480 participants will be randomly assigned to either an aspirin group, a Xuesaitong group, or drug combination group at a ratio of 1: 1: 1. Participants in the aspirin group will be administered aspirin (100 mg, qd) orally 30 min after breakfast, participants in the Xuesaitong group will be administered Xuesaitong soft capsule (contains PNS and excipients; 200 mg, tid) orally 30 min after breakfast, and participants in the drug combination group will be administered both drugs above. The two drugs should be taken half an hour apart, and aspirin should be taken first. All treatment courses will last for 30 days. Blood samples will be acquired 30 min before administration on day 1 and 30 min after administration on day 30. The volume of each blood sample is 4 mL. And fecal samples will be collected on days 1 and 30. Details of patient follow-up are summarized in Table 1 and Figure 1.

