Xuesaitong, a marketed Chinese medicine with the main active component of PNS, has been widely and long-term used to prevent and treat hematological diseases and cardiovascular diseases [23]. Several clinic trials indicated that Xuesaitong could inhibit platelet activation in patients with blood hyperviscosity syndrome [24]. Interestingly, as for the widespread clinical application together with aspirin, many clinicians found its ability to protect against gastrointestinal injury. In view of this protective efficacy, some researches have shown that Xuesaitong could enhance the proliferative ability of human endothelial cells to heal the wound and stop bleeding [25]. Our previous studies demonstrated Xuesaitong can alleviate gastrointestinal injury caused by aspirin in rats [13]. Combined with HE staining results, our results indicate that the protective mechanism of Xuesaitong on aspirin-induced gastrointestinal injury may act through increasing VEGFA and protecting gastrointestinal mucosa. As for Xuesaitong's ability that both effectively guarantee the clinical efficacy of aspirin and prevent gastrointestinal injury, it is worthwhile to further study the mechanism of the combination of these two drugs and supply a rational combination. Since we have proved that aspirin and Xuesaitong could increase the AUC of each other [11, 12], this means the content of effective drugs in the blood increased. In order to achieve the same blood concentration, the intake of aspirin might be reduced, the adverse reaction might also reduce accordingly. To explore the possibility of reducing the dose of aspirin, it is worth making clear the efficacy and safety of the combination of aspirin and Xuesaitong. By using this randomized controlled noninferiority trial, determining the clinical efficacy indexes like aggregation rate, platelet membrane glycoprotein indexes, and gastrointestinal injury indexes like calcitonin activity and I-FABP allows us to find out whether the platelet aggregation in patients was excessively inhibited and whether the digestive tract injury caused by aspirin is alleviated under drug combination.

In conclusion, the results of this study are expected to provide evidence of high methodological quality on the synergy effect of combination of Xuesaitong and aspirin for CHD synergy effect of combination of Xuesaitong and aspirin.

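### The trial is labelled noninferiority, but its aim is superiority and its reported tests are difference tests without a margin, so a non-significant result cannot support the title's conclusion

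*Protocol article*

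**What the plan says.** **Label.** The title ends "Study Protocol for a Randomized Controlled Noninferiority Trial", and the Discussion again calls the trial noninferiority. The design statement in section 2.1 names neither noninferiority nor superiority.

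**Aim.** The last paragraph of the Introduction describes a "randomized controlled noninferiority trial to explore whether the efficacy and safety of combination for CHD patients are superior to the single use".

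**Promised conclusion.** The Abstract expects evidence on "the synergy function of Xuesaitong and aspirin upon the antiplatelet and anti-gastrointestinal injury effect for CHD". The Discussion closes by expecting "evidence of high methodological quality on the synergy effect of combination of Xuesaitong and aspirin".

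**Arms.** Participants go to an "aspirin group, Xuesaitong group, and drug combination group", allocated 1:1:1.

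**Sample size (section 2.4).** Platelet aggregation is assumed to be 38.72% on aspirin and 37.79% on Xuesaitong. With type I error 0.05 and type II error 0.2 this is said to need 131 per arm, raised to 160 for 20% dropout. No SD, margin, sidedness or value for the combination arm is reported.

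**Analysis (section 2.10).** Continuous outcomes are compared by t-test or Wilcoxon test, categorical outcomes by Fisher's exact test and adverse events by chi-squared test. A Cox model gives a hazard ratio with a 95% confidence interval. The decision threshold is P < 0.05: "two-sided) was considered to be statistically significant".

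**The concern.** Noninferiority and superiority are different hypotheses and need different decision rules. A noninferiority conclusion needs a margin and a confidence limit that excludes it. A superiority conclusion needs a significant difference in the right direction. The article gives the first label, the second aim, and a rule that serves only the second.

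What the trial may conclude is at stake. If the combination does not differ significantly from a single drug, the title points to a claim of noninferiority that nothing in the reported design or analysis would support.

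A secondary issue is that synergy is promised but never defined. If it is read as more than the sum of the two drugs' effects, these three arms cannot show it.

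**Working it through.** **1. Can the stated sample size supply a noninferiority rule?**

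The inputs from section 2.4 are 38.72% and 37.79% (difference 0.93 points), alpha 0.05, power 0.80 and 131 per arm. The figure of 131 cannot be reproduced from these, because neither an SD nor a margin is given. Working backwards:

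- *Difference in means.* n = 2·SD²·(z_α + z_0.80)²/0.93². Setting n = 131 requires SD = 2.69 (two-sided 0.05) or 3.03 (one-sided 0.05). Neither is stated.
- *Difference in proportions.* Two-sided 0.05 needs 42,870 per arm.
- *Noninferiority of proportions.* With both rates at 38.72%, one-sided 0.05 and an assumed 15-point margin: 2 × 0.3872 × 0.6128 × (1.645 + 0.842)²/0.15² ≈ 130.4, or 131. This is a back-fit: the article states neither the margin nor the sidedness, and other margins fit under other assumptions (about 14 to 18 points).

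In every case the calculation compares aspirin with Xuesaitong. The combination, which the aim concerns, does not enter.

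**2. Can section 2.10 supply one?**

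The tests are of no difference. The only confidence interval belongs to a Cox hazard ratio, which has no margin and no matching time-to-event outcome in Table 4. So no stated criterion yields noninferiority as a conclusion of its own.

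**3. What the rule can and cannot show.**

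Lower aggregation and lower calprotectin are taken as better. A significant result for the combination puts the upper limit of the 95% interval for combination minus single drug below 0, and hence below any positive margin. Superiority therefore implies noninferiority. A non-significant result only says that the interval includes 0.

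The half-width of that interval is 1.96·SD·√(2/131). No SD is given, so a range is assumed. The last column is 1 − Φ(2/(SD·√(2/131)) − 1.96), for a combination truly 2 points worse (also assumed).

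| Assumed SD (points) | 95% CI half-width (points) | Chance of P > 0.05 if truly 2 points worse |
|---|---|---|
| 5 | 1.21 | about 10% |
| 10 | 2.42 | about 63% |
| 15 | 3.63 | about 81% |

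**4. What 131 per arm would support as a noninferiority trial.**

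For means, one-sided 0.025, 80% power and no true difference:

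margin = (1.960 + 0.842)·SD·√(2/131) = 0.346 SD.

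That is 1.73, 3.46 or 5.19 points for SD 5, 10 or 15. Power is Φ(margin/√(2/131) − 1.96), with the margin in SD units:

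| Margin (SD) | Power at 131 per arm |
|---|---|
| 0.20 | 37% |
| 0.30 | 68% |
| 0.346 | 80% |
| 0.50 | 98% |

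Under the same true equality, the stated two-sided rule favours the combination 2.5% of the time.

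**5. Synergy (secondary).**

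The additive interaction is combination − aspirin − Xuesaitong + neither. The fourth term has no arm. Baseline does not replace it: inclusion criterion 6 requires at least a year of regular aspirin and the article describes no washout. With a fourth group of 131, the standard error would be √(4/131) = 0.175 SD, against √(2/131) = 0.124 SD for a pairwise contrast.

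**The case against.** Several objections have force.

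- **A reader might infer that the trial can never establish noninferiority.** The documents do not support that. As shown above, a significant result favouring the combination implies noninferiority. The gap is confined to results that are not significant.
- **A reader might infer that no margin exists.** The article condenses a fuller protocol, and the analysis plan is not shown, so a margin may be recorded elsewhere. The fair statement is that none is reported beside the sample-size calculation, where it would be a necessary input. The clash between label and aim is on the page regardless.
- **A reader might infer that the synergy claim is unreachable.** That holds only if synergy means more than additive, and the article never defines it so. Its aim is superiority to single use, and Table 4 groups outcomes under improving efficacy and reducing gastrointestinal side effects. If synergy means better than each drug alone, three arms suffice. This part is a matter of wording.
- **The consequence is not certain.** Nothing in the article says that P > 0.05 will be read as noninferior. The chances in the table (10% to 81%) rest on an assumed SD and an assumed 2-point difference, and they illustrate a principle. They are not a forecast for this trial.

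None of this reconciles the noninferiority label with the superiority aim, or provides a rule for the conclusion the title names.

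**Conclusion.** The point holds at this scope. The label and the aim contradict each other, the sample-size statement reports neither a margin nor an assumption for the combination, and the stated analysis is difference testing only. The trial as written can conclude superiority of the combination, and noninferiority only by way of it. A non-significant result has no route to the conclusion in the title.

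This does not depend on any assumed SD. The only figures that do are the margins in points and the table of chances. The 0.346 SD margin assumes 131 evaluable per arm, one-sided 0.025, 80% power and no true difference.

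The label and aim need correcting because they determine what may be claimed. The synergy wording is secondary.

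**What to change.** **Preferred.** Remove the noninferiority label from the title, Introduction and Discussion. State the hypothesis as superiority of the combination over each single drug on platelet aggregation and calprotectin. This matches the Introduction's aim and the tests in section 2.10. The cost is wording, and the relabelling itself adds no patients. It does not show that 131 per arm is adequate, so section 2.4 should still state what is assumed for the combination.

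**If noninferiority is truly intended for platelet aggregation.** State four things:

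- which comparison it applies to;
- its direction, since the Discussion also asks whether aggregation is inhibited too much;
- a justified margin;
- a confidence-limit rule, followed by a superiority test in sequence.

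Because the trial is open-label, fix these before anyone examines outcome data by arm. Restate the sample size for the chosen margin: 131 per arm is enough for 80% power only at about 0.35 SD or wider, and a tighter margin needs more participants.

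**In either case.** Define synergy as better than each single drug, or replace the word with combination versus each single drug. This costs only wording.
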